## Abstract

**Background:**

During the last decade, research has shown that besides the known predictive factors, such as duration of subfertility, a women’s age, the body mass index, also the microbiome might affect fertility. Micro-organisms together with their genetic information and the milieu in which they interact are called the microbiome. Studies have shown that the presence of certain microbiota during assisted reproductive technology (ART) has a positive impact on the outcome. However, the potential role of using the microbiome as a predictor for outcome of ART has not yet been investigated.

**Methods:**

In a prospective study, 300 women of reproductive age and with an indication for in-vitro Fertilization (IVF) with or without Intra Cytoplasmic Sperm Injection (ICSI) treatment will be included. Prior to the IVF or IVF-ICSI treatment, these women provided a midstream urine sample and a vaginal swab. The composition of the urinary and vaginal microbiome will be analysed with both Next Generation Sequencing and the IS-pro technique. The endpoints of the study are pregnancy achieved after fresh embryo transfer (ET) and within the subsequent year after inclusion. External validation of the findings will take place in an additional cohort of 50 women with an IVF or IVF-ICSI indication.

**Discussion:**

In the proposed study, the predictive accuracy of the composition of the urinary and vaginal microbiome for IVF or IVF-ICSI outcome will be only validated for fresh ET. Follow-up has to show whether the predictive accuracy will be similar during the consecutive frozen ET’s as part of the IVF or IVF-ICSI treatment or for subsequent stimulated or natural cycles. In addition, external validation will take place in another cohort and hospital. Predictive knowledge of the microbiome profile may enable couples to make a more substantiated decision on whether to continue treatment or not. Hence, the unnecessary physical and emotional burden of a failed IVF or IVF-ICSI treatment can be avoided.

**Trial registration:**

ISRCTN ISRCTN83157250. Registered 17 August 2018. Retrospectively registered.

## Plain English summary

In-vitro Fertilization (IVF) with or without Intra Cytoplasmic Sperm Injection (ICSI) is often the only option for subfertile couples that want to have children of their own. These treatments might cause considerable psycho-social stress and physical complaints. In this study we investigate whether we can predict IVF or IVF-ICSI outcome based on the vaginal bacteria which are carried by the women themselves.

Participants will be asked to self-collect a urine sample and a vaginal sample prior to the start of their IVF or IVF-ICSI treatment. The composition of the present bacteria will be analysed and linked to the fertility treatment or pregnancy outcome.

The objective of this study is assessment of the accuracy of a predictive algorithm based on the bacteria present in and on the woman herself. In addition, we will validate this predictive algorithm in an external population.

In conclusion: predictive knowledge based on the present bacteria may enable couples to make a more substantiated decision on whether to continue fertility (IVF or IVF-ICSI) treatment or not.

## Background

Assisted Reproductive Technologies (ART) such as in-vitro Fertilization (IVF) [1] with or without Intra Cytoplasmic Sperm Injection (ICSI) [2] are used to assist the 10–15% of couples affected by subfertility [3]. At present the pregnancy rate is around 25% for the first attempt (cycle) and cumulative ongoing pregnancy rates after additional cycles vary between 40 and 50% depending on the number of treatment cycles [4, 5]. Because of the psychosocial, physical and financial burden of ART, prediction of accurate outcome is needed. Current prediction models perform moderately well and are based upon pure clinical parameters such as age, number of previous failed IVF treatments, and the cause of subfertility [6].

However, at the department of Urology and the division of Reproductive Endocrinology and Infertility of the department of Obstetrics & Gynaecology both in the Erasmus University Medical Centre, a new predictive algorithm for the outcome of IVF or IVF-ICSI based on the microbial composition (population of different bacteria in a given sample) has been developed. The collection of microorganisms that live on or in the human body is known as our microbiota and its complete genetic profile as the microbiome. For this study, the urinary microbiome was determined in mid-stream urine sample. All urine samples were collected prior to the start of the actual IVF or IVF-ICSI treatment [7].

The predictive algorithm was developed in a pilot study comprising 42 women who were expected to start with either IVF or IVF-ICSI treatment and uses the percentages of the species *Lactobacillus*, *Staphylococcus* and *Escherichia coli* within the total microbiome of the sample. In the pilot study, the composition of the urinary microbiome prior to the start of the IVF or IVF-ICSI treatment was linked to the outcome of the ART treatment defined as ongoing pregnancy after one treatment cycle and pregnancy rates within 1 year after the initiation of the treatment. Cluster analysis and principal component analysis revealed that based on the microbiome composition it is possible to separate (by means of clustering) the women into two clusters: pregnant and non-pregnant women. After logistic regression, the bacterial species that dominated this prediction were identified and those were used to construct a predictive algorithm. In the pilot study, the test panel had a specificity of 96% and a sensitivity of 81%. Importantly, by adding the species *Bacillus RG4* the specificity improved up to 100%. The species found to be predictive has still to be confirmed in an independent, separate study. The crucial outcome of this predictive test is its specificity or better said, the prediction that the treatment will not result in pregnancy, since it could be used to select those women who should not be subjected to treatment because they will have a high chance not getting pregnant.

Hypotheses that might explain these finding is that the microbiome, acts as a sensor for the immunological tolerance that exist in secretory epithelia of a particular woman. Hence, it constitutes a proxy for endometrial receptivity which in turn depends on a similar immune response towards the developing embryo which is trying to implant. Another hypothesis is that the bacterial species included in the predictive algorithm possibly thrive the nutritional environment within epithelial secretions, which might be essential for initial survival of the embryo after transferral into the uterine cavity [8, 9].

In line with our finding that the genus *Lactobacillus* has an important role in reproductive health/outcome, are similar results of several published studies [10–20]. Recent publications show that women with infertility problems have a reduced number of *Lactobacillus* compared to healthy women [10–18]. Moreover, the presence of non-*Lactobacillus* dominated microbiota (e.g. presence of the genera *Gardnerella* and *Streptococcus*) seems to be associated with significant decreases in implantation, ongoing pregnancy and live birth rates [17] and clinical pregnancy rates [19, 20].

The large benefit of such a predictive test might have for patients undergoing IVF or IVF-ICSI treatment necessitates validation of these findings in a larger study with several independent ART clinics. Furthermore, to allow future clinical application of the algorithm, the Sanger sequencing technique used in the pilot study needs to be replaced by a quick and high-throughput method. Therefore, all collected microbiome samples will concomitantly be investigated with a Next Generation Sequencing (NGS) method as well as with the polymerase chain reaction (PCR) based IS-pro technique. These techniques will be used for both urine samples and vaginal samples, to investigate whether the urinary microbiome is affiliated from the vaginal microbiome. Here we describe the design of the ReceptIVFity cohort study.

## Methods

### Study aim

With ReceptIVFity, we aim to validate the algorithm in a larger cohort, and to develop a predictive test suitable for the use in daily practice. In this cohort study, the following aims will be addressed:

Primary Objective:To assess the specificity and sensitivity of the urinary and vaginal microbiome composition for the prediction of embryo implantation failure of a consecutive IVF or IVF-ICSI procedure.

Secondary Objective:To assess the specificity and sensitivity of the urinary and vaginal microbiome composition for the prediction of the cumulative outcome of 1 year of subsequently performed IVF or IVF-ICSI procedures.

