### Study population

Women who will visit the infertility outpatient clinics of participating hospitals and who are expected to undergo their first IVF or IVF-ICSI cycle within the next 2 months will be approached to participate in this study. Inclusion criteria to be fulfilled are: women aged between 20 and 44 years and a male partner. Those excluded from the study will be: women with an indication for emergency IVF because of cancer or other reasons, endometriosis American Fertility Score (AFS) III/IV and pre-treatment with a Gonadotrophin-releasing hormone (GnRH) analogue or those who use hormonal contraceptives within 3 months prior to the start of their IVF or IVF-ICSI intake. Those women who are using the oral contraceptive pill for the purpose of cycle timing prior to their treatment cycle will be eligible for this study. Women who have had a previous pregnancy or miscarriage in their medical history will also be excluded from participation. Pregnancy outcomes after the first fresh ET will be used as endpoint for this study. Ongoing pregnancy is defined as an intrauterine embryo/foetus with detection of cardiac activity on transvaginal ultrasound between 7 and 9 weeks of gestation.

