### Strengths

The ReceptIVFity study will be the first cohort study in which the microbial composition will be used as predictor for IVF or IVF-ICSI outcome prior to the start of the treatment. As mentioned in the background section, several studies have found associations between the presence of microorganisms and reproductive outcomes, such as decreased implantation, pregnancy, ongoing pregnancy, and live birth rates. However, the clinical applicability of these findings has not yet been integrated into daily practice.

The ReceptIVFity cohort study consists of a large patient group/sample size and well-defined patients. A large sample is indicated, anticipating the fact patients can drop out for further treatment/follow up due to several reasons, such as poor response or total fertilisation failure. The included patients with embryo transfers will be used to investigate an association between microbial composition and IVF or IVF-ICSI outcome.

A prospective study design blinded for the test result, avoids bias to continue or not continue the treatment and allows for unbiased follow-up of the treatment outcomes.The 1 year follow-up is needed to examine the sustainability of the predicted outcome and will provide insight into the possibilities of becoming pregnant with subsequently performed IVF or IVF-ICSI procedures. Different techniques can be used to assess the microbiome and a high throughput technique is desirable for future application in daily practice. The prospective study validates the findings from the pilot study by the use of two different techniques. NGS that has become a gold standard for categorising bacteria or characterising microbial communities and the IS-pro technique which has the benefit of presenting results within 5 hours will be compared in this study. In addition, two sample sites (urine samples and vaginal swabs) will be compared with each other, both sites are easy to obtain by patients themselves. Developing a predictive test based on the urogenital microbiome composition will contribute to a personalised medicine approach in the future.

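### The 1-year cumulative outcome most naturally includes the first-transfer pregnancies, so it cannot by itself show whether the prediction is sustained in later transfers and cycles

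*Protocol article*

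**What the plan says.** The primary endpoint is tied to the first transfer: "Pregnancy outcomes after the first fresh ET will be used as endpoint for this study" (Protocol article, Study population). The secondary objective is sensitivity and specificity for the "prediction of the cumulative outcome of 1 year of subsequently performed IVF or IVF-ICSI procedures" (Study aim).

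The abstract's Methods paragraph describes the two endpoints as "pregnancy achieved after fresh embryo transfer (ET) and within the subsequent year after inclusion". Women are approached when they are "expected to undergo their first IVF or IVF-ICSI cycle within the next 2 months" (Study population) and are sampled before treatment starts (Study materials). The pilot's 1-year outcome was "pregnancy rates within 1 year after the initiation of the treatment" (Background), a window that also contains the first cycle.

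Two places say what the follow-up is for. Under Strengths: "The 1 year follow-up is needed to examine the sustainability of the predicted outcome". In the abstract's Discussion paragraph: "Follow-up has to show whether the predictive accuracy will be similar during the consecutive frozen" transfers, and in subsequent stimulated or natural cycles.

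**The concern.** Whether a prediction is sustained is a question about what happens after the first transfer. A cumulative outcome counted from inclusion mixes that with the first-transfer result. A woman who conceives at the first transfer is a success on both outcomes, so the 1-year sensitivity and specificity partly restate the primary result. If the profile were informative at the first transfer and uninformative afterwards, the 1-year table would still show an association, and someone looking for sustainability could take it as partial persistence.

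The definition is also unsettled. Study aim refers to IVF or IVF-ICSI procedures. The abstract's Methods paragraph refers to pregnancy within a year of inclusion without saying how it was conceived. The abstract's Discussion paragraph brings in natural cycles. These differ in which pregnancies count, and Study aim gives no time origin.

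At stake is the interpretation of the secondary objective. The primary analysis is not affected.

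**Working it through.** **Inputs.** First-attempt pregnancy rate p1 = 0.25 and cumulative rate c = 0.40 to 0.50 (Background). Pilot sensitivity 0.81 and specificity 0.96 (Background). Cohort of 300 women (abstract, Methods). The plan states no expected 1-year accuracy, so there is no figure of its own to reproduce. An unfavourable profile is the positive test, and failure to become pregnant is the condition predicted.

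**Model assumptions.** All 300 women have a first fresh transfer. The 25% applies to that transfer and the 40–50% applies at 1 year. After the first transfer, pregnancy is unrelated to profile, with probability q = (c − p1)/(1 − p1), that is 0.15/0.75 = 0.20 to 0.25/0.75 = 0.33 in both profile groups.

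**1. Overlap.** The share of 1-year pregnancies that are first-attempt pregnancies is s = p1/c: 0.25/0.40 = 62.5% to 0.25/0.50 = 50%.

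**2. What carries over.** With Se and Sp the first-transfer sensitivity and specificity:
- All women not pregnant at 1 year failed the first transfer, so cumulative sensitivity = Se.
- Pregnant women are a mixture, so cumulative specificity = s × Sp + (1 − s) × (1 − Se).
- Adding the two and subtracting 1 gives cumulative J = s × (Se + Sp − 1) = s × first-transfer J.

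With no later prediction at all, 50–62.5% of the first-transfer Youden index remains.

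**3. Pilot values.** First-transfer J = 0.81 + 0.96 − 1 = 0.77.
- c = 0.40: specificity = 0.625 × 0.96 + 0.375 × 0.19 = 0.67; J = 0.48.
- c = 0.50: specificity = 0.5 × 0.96 + 0.5 × 0.19 = 0.575; J = 0.385.

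If the two pilot figures are swapped between the labels, J is the same.

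**4. A rule that flags fewer women.** Suppose it flags 4% of first-transfer pregnancies (the pilot specificity) and 30% of everyone else. The 30% is an assumption and is not in the document. The flagged fraction is 0.25 × 0.04 + 0.75 × 0.30 = 0.235. Flagged and pregnant at 1 year is 0.25 × 0.04 + (c − 0.25) × 0.30, that is 0.055 (c = 0.40) or 0.085 (c = 0.50).

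| Outcome | Pregnant, unfavourable | Pregnant, favourable | Odds ratio | Specificity |
|---|---|---|---|---|
| First transfer | 0.010/0.235 = 4.3% | 0.240/0.765 = 31.4% | 0.10 | 96% |
| 1 year, c = 0.40 | 0.055/0.235 = 23.4% | 0.345/0.765 = 45.1% | 0.37 | 86% |
| 1 year, c = 0.50 | 0.085/0.235 = 36.2% | 0.415/0.765 = 54.2% | 0.48 | 83% |

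The true odds ratio after the first transfer is 1 in both 1-year rows.

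**5. How often it would look significant.** In 10,000 simulated cohorts of 300, a two-sided 5% test of 1-year pregnancy by profile rejected in the shares below. Only the first row uses pilot values; the other accuracies are assumed.

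| Se / Sp at first transfer | c = 0.40 | c = 0.50 |
|---|---|---|
| 0.81 / 0.96 | about 100% | about 100% |
| 0.25 / 0.96 | 82% | 64% |
| 0.30 / 0.90 | 70% | 52% |
| 0.30 / 0.80 | 21% | 17% |

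If the rule predicts nothing at the first transfer either, cumulative J is 0.

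**6. The conditional comparison.** Restricted to women not pregnant after the first transfer, J is 0 in all these scenarios and the same test rejected in 4.7% to 5.4% of simulations, as it should.

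**The case against.** Four points can fairly be made for the plan.

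- *Subsequently performed*, used in Study aim and again under Strengths, can be read as leaving out the first procedure. This stands as an ambiguity. The word *cumulative*, the year counted from inclusion and the pilot's definition all point towards including it.
- The abstract's Discussion paragraph asks about accuracy at later transfers and cycles, which is close to the analysis proposed here, and an article may leave the split of the 1-year data to a fuller document. That is fair, and the absence of such a split is not the complaint. The point is that the only 1-year outcome the article defines does not match the inference it names.
- A reader might infer that the 1-year result is bound to look like lasting prediction. The document does not support that. Carry-over is diluted: in the example the odds ratio moves from 0.10 to 0.37–0.48 and specificity from 96% to 86–83%; at pilot values specificity falls to 67–57.5%. Many would read that as deterioration. In the unfavourable group, 82–88% of the 1-year pregnancies (0.045/0.055 to 0.075/0.085) arise after the first transfer, so that group's rate mostly reflects later events.
- A reader might also infer that the test is meant for the decision after a failed cycle, and that the cumulative outcome should be reduced to description. The text speaks of continuing treatment but never of a failed cycle. The Discussion and the closing summary place the test before treatment starts, and for that decision the cumulative 1-year chance is a legitimate target.

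**Conclusion.** The point holds in a limited form. The 1-year outcome most naturally contains the first-transfer pregnancies, and a cumulative outcome of that kind cannot separate lasting prediction from a first-transfer effect carried forward. With the protocol's background rates the carried-over part is 50–62.5% of the first-transfer Youden index. Whether it looks convincing depends on the first-transfer accuracy: near-certain significance at pilot values, about one study in five or six for an assumed rule with sensitivity 0.30 and specificity 0.80, and no carry-over if the rule does not work at the first transfer.

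This rests on three assumptions: first-transfer pregnancies count at 1 year, the background rates apply to this cohort and to a 1-year window, and all women have a transfer. Fewer transfers would lower the power but not change the relation between the two Youden indices. The differing descriptions of the time window and of the pregnancies that count need reconciling whichever reading is meant.

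**What to change.** 1. Keep the cumulative 1-year sensitivity and specificity as the secondary outcome, described as information for counselling before treatment.
2. Add an analysis by profile among women who had a first fresh transfer without ongoing pregnancy, using pregnancies from later fresh and frozen transfers and showing natural conceptions separately. Base any statement on sustainability on this analysis.
3. State one time origin and one list of countable pregnancies, in the same words in the abstract's Methods paragraph and in Study aim, and say whether the first transfer counts.

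The cost is one further analysis of follow-up data already planned, plus the wording change. The drawback is precision: the denominator is at most about 300 × 0.75 = 225 women, fewer if some have no fresh transfer (Strengths expects losses from poor response or total fertilisation failure), so intervals will be wider.

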### Study design and setting

The prospective study of the urogenital microbiome of subfertile women of reproductive age will be carried out in eight IVF centres in the Netherlands. The participating centres are: Erasmus University Medical Centre (UMC) (Rotterdam), Radboud UMC (Nijmegen), UMC Utrecht (Utrecht), VU University Medical Centre (Amsterdam), Isala Fertility Centre (Zwolle), Sint Elisabeth Hospital (Tilburg), VivaNeo Medical Centre Kinderwens (Leiderdorp), and Maastricht UMC+ (Maastricht). Inclusions will take place over the period from the 1st of June 2015 until the 31st March 2016. The external validation cohort will exist of women from the Dutch division of the MVZ VivaNeo Kinderwunschzentrum Düsseldorf GmbH (Germany) and inclusions will take place throughout 2018.

### Study population

Women who will visit the infertility outpatient clinics of participating hospitals and who are expected to undergo their first IVF or IVF-ICSI cycle within the next 2 months will be approached to participate in this study. Inclusion criteria to be fulfilled are: women aged between 20 and 44 years and a male partner. Those excluded from the study will be: women with an indication for emergency IVF because of cancer or other reasons, endometriosis American Fertility Score (AFS) III/IV and pre-treatment with a Gonadotrophin-releasing hormone (GnRH) analogue or those who use hormonal contraceptives within 3 months prior to the start of their IVF or IVF-ICSI intake. Those women who are using the oral contraceptive pill for the purpose of cycle timing prior to their treatment cycle will be eligible for this study. Women who have had a previous pregnancy or miscarriage in their medical history will also be excluded from participation. Pregnancy outcomes after the first fresh ET will be used as endpoint for this study. Ongoing pregnancy is defined as an intrauterine embryo/foetus with detection of cardiac activity on transvaginal ultrasound between 7 and 9 weeks of gestation.

### Study materials

A vaginal swab and a midstream urine sample before the start of the IVF or IVF-ICSI procedure will be self-collected. The swab and the urine sample have to be taken within the 2 months prior to the ET. A self-collecting method was chosen, because it is minimally invasive and therefore suitable for use in daily practice. Vaginal samples will be taken with FLOQSwabs™ (Copan Italia SpA, Brescia, Italy). The participants will be instructed to insert the swab 3–5 cm beyond the vaginal orifice, and move the swab around along the vaginal wall for 10–15 s. After this procedure the swabs will be immediately placed in Eppendorf tubes filled with reduced transport fluid (RTF) buffer (Microbiome Ltd., Amsterdam, the Netherlands). Until further processing, samples will be stored in a freezer at − 20 °C degrees.The urine sample collection will be obtained according to a standard ‘clean catch’ protocol, including washing hands thoroughly, cleaning the urinary opening with towelettes and collecting a midstream specimen in a sterile container. The urine sample will be stored at room temperature or in the refrigerator at 2–8 °C for a maximum of 2 hours until further processing. Further processing will consist of vortexing the urine sample and centrifuging 10 ml of the urine at 1500 relative centrifugal force (RCF) followed by resuspension in 1 ml of urine, which will be stored at -20 °C degrees until transport.Next, vaginal swabs and urine samples will be transported on dry ice by courier from the eight clinics to the microbiological laboratory.

